#### Nested qualitative study

We will recruit GP/patient dyads at the intervention study sites to increase our understanding of the impact of eCDS use or non-use on the consultation. We will interview, within 6 weeks of consultation, up to 30 patients for whom the tool has been used for assessment of their symptoms, or where the tool was not used despite relevant symptoms, to gain a richer understanding of the impact of the use or non-use of the eCDS on the consultation. Consent will be sought from patients to be interviewed as part of the original participation consent form. The research team will screen the patients who have consented to be interviewed to purposively sample for eRAT use and non-use. The researcher will also match consenting patients with their GP to identify GP/patient dyads.

These GPs will have been provided with information about the nested qualitative study at the point of practice recruitment. GPs subsequently selected to take part in an interview will be contacted by telephone to confirm that they are willing to be interviewed and to arrange a suitable date and time for the interview to take place. GPs who are interested in participating will provide consent to participate. If these GPs are unable to find the time for a face-to-face interview, they will be offered the option of a telephone interview. We will undertake semi-structured interviews with as many as possible of the GPs matched with their patients (up to 30).

We will also interview up to a further 10–15 GPs in order to identify and gain an understanding of the facilitators and constraints influencing the implementation and use of eCDS in clinical practice. GPs will be recruited purposively to sample as widely as possible (gender, age, trainer status, and frequency of eRAT use) and will include GPs in the intervention practices who did not use eCDS during the study. The interview schedule will be based on normalisation process theory.

At the end of their interview, all GPs will be asked if they are willing to take part in further interviews by telephone 3 months and 1 year later. If they agree to do so, they will be contacted after 2 months to confirm that they are still willing and to arrange a suitable date and time for the interview to take place.

Data provided by patients will remain confidential and will not be shared with their GP, and GP data will also not be shared with patients. Both patients and GPs will provide written consent prior to interviews commencing. GPs who are interviewed by telephone will be asked to provide verbal consent at the beginning of the interview and also complete a written consent form to be returned by post. Data will be audio-recorded and transcribed professionally.

### Data analysis

#### Statistical analysis

Patient throughput will be summarised for the 16-month recruitment period. For *each trial arm,* we will record the (1) number of eligible patients, (2) number of eligible patients approached to take part in the study, (3) number of eligible patients that consented/are recruited to the trial, and (4) number of recruited patients for whom outcome data are collected.

We will report the percentage of all eligible patients who are recruited (participation percentage) and the percentage of recruited patients for whom outcome data are collected with 95 % confidence intervals. Separate reporting of the participation percentage by the trial arm will help identify any obvious recruitment bias resulting from randomising the practices before recruiting patients to the trial. However, we consider the risk of serious recruitment bias to be low because all eligible participants from intervention or control practices will be invited to participate, and this will be done by post after the index consultation, rather than during the consultation.

General practices in the intervention and usual-care arms will be described separately with respect to region (a factor used to balance the randomisation). Participating patients will be described separately within each trial arm with respect to relevant baseline demographic characteristics, using means and standard deviations (or medians and interquartile ranges) for continuous variables and percentages for categorical variables. No formal tests of significance will be used for these descriptive analyses.

It is not a primary objective of the study to obtain definitive estimates of the intervention effect on study outcomes. However, comparisons between the intervention and control arms using the intention--treat principle will be reported as ancillary analyses. A comparison of binary outcomes will be implemented using marginal logistic regression models using generalised estimating equations (GEEs) with information sandwich (‘robust’) estimates of standard error, specifying the correlation structure as exchangeable. In the case of rare binary events, the responses will be summarised using percentages only. Comparison of time-to-event outcomes will be carried out using marginal proportional hazards models with information sandwich (‘robust’) estimates of standard error.

Binary outcomes will be reported using a percentage for each trial arm, an odds ratio for comparing the trial arms, a 95 % confidence interval, and *p*-value. Time-to-event outcomes will be presented as the hazard ratio, confidence interval, and *p*-value. Crude estimates of intervention effect and estimates adjusted for region and practice size will be presented. The following outcomes will be compared:For all patients○ Whether the patient is referred (binary)For all referred patients○ Whether the patient is referred via the 2-week wait pathway (2WW) (binary)○ Whether patient is referred via the direct-access pathway (binary)○ Whether the referred patients were diagnosed with cancer (conversion – binary outcome)For all patients with cancer○ Whether the diagnosed patients had been referred via the 2WW/direct-access pathway (binary outcome)For patients referred via the 2-week wait○ Cancer conversion rate (binary outcome)For patients referred via the direct-access pathway○ Cancer conversion rate – (binary outcome)For patients diagnosed with cancer○ Stage at diagnosis○ Treatment with curative intent (binary outcome),○ 1-year and 3-year survival○ Diagnostic interval (time from symptomatic presentation to cancer diagnosis)

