### Sample size

This phase II trial is not powered to test specific hypotheses but to provide sufficient process data and enough participants with G-O cancer to provide estimates of effect to inform a phase III trial. We will recruit 60 practices with 1:1 randomisation, allocating 30 to each of the intervention and control arms. We anticipate that 64 patients (32 in each arm) who are subsequently diagnosed with G-O cancer will participate over the 16-month recruitment period, based on the following assumptions: (1) 17 out of every 1000 people more than 55 years of age undergo diagnostic gastroscopy for new upper gastrointestinal (GI) symptoms each year [1]; (2) 2.1 % [7] to 5.5 % (Trent Cancer Registry, personal communication) of these will have G-O cancer, depending on the route of referral (we have assumed 4 %); (3) the average practice size is 6500, with 28 % of the patients being older than 55 years of age [28], which implies that 1800 patients in each practice are age 55+; (4) 80 % of those with the index symptoms will be identifiable through READ codes (our own experience); and (5) the consent rate in the study population is 80 %. To illustrate the recruitment requirements, the number of patients with a new upper GI symptom annually ranges from 28–40/1000 [29]. Thus, from 30 control practices, we expect 1292–1843 participants, 780 diagnostic gastroscopies, and 32 patients with G-O cancer.

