### Intervention

Intervention practices will be provided with a modified version of the Macmillan eCDS tool on the BMJ Informatica platform, which will contain the G-O cancer eRAT (Fig. 1) embedded within the clinical system. This provides a drop-down box containing an interactive risk calculator, which can be opened at the GP’s discretion during the consultation. It allows additional symptoms to be entered and generates a value for the risk of a currently undiagnosed G-O cancer. The GP then decides on further management, which may be clinical review in primary care, referral to a GI specialist, or direct referral for gastroscopy. The G-O cancer eCDS will also display an on-screen prompt at the start of a consultation if the relevant symptom(s) with a total risk >2 % has (have) been entered within the previous 12 months. Macmillan has undertaken extensive development and has addressed many of the key issues identified in the systematic reviews of eCDS, particularly the problem of prompt fatigue [23].

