### Data collection procedures

#### Patient recruitment

Practice administrative staff will use a pre-specified search string to search their electronic medical records weekly in order to identify patients who have presented to a GP within the previous week with qualifying symptoms. The records of patients thus identified will be reviewed by a designated individual (GP or practice research nurse) to determine eligibility to take part in the study. Administrative staff will post or use Docmail to send an information pack (consisting of invitation letter, participant information sheet, consent form and a reply paid envelope) to eligible patients.

We will seek consent for access to primary and secondary care records for follow-up data and for qualitative interviews. Patients who wish to participate will return their completed consent forms to the research centre. The researcher will inform the practice if a consent form is received and whether consent was given for data to be used in the study. For those who consent to their data being used in the study, the practice will respond with the date of the index consultation and, in addition, for those in the intervention arm, will submit an age group (in 5-year increments of 55–59, 60–64, 65–69, 70–74, 75–79, 80–84, 85–89, and 90+), the gender, and whether or not the eRAT was used.

A database of patients identified by the search string and those invited to participate will be kept by each practice; this database will be updated on a weekly basis. Practice administrative staff will identify any patients who have not responded at 2 weeks after being sent the invitation. These patients will be sent a reminder letter using either post or Docmail. Further information on the process of patient recruitment is provided in Table 1.

**Table 1 Tab1:** Patient recruitment procedures

Step	Frequency	Person responsible
Patient consults with relevant symptom		
Search of computer records to generate list of patients with qualifying symptoms	Weekly	Practice admin staff
List reviewed for eligibility and exclusions	Weekly	Practice research nurse
Invitations sent	Weekly	Practice admin staff
Response from patient received by researcher		Researcher
Consent information to practice	Weekly	Researcher
Date of index consultation identified for each consenting patient sent to researcher	Weekly	Practice research nurse

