#### Data collection

Academic research staff will visit GP practices every 6 months to extract data on participating patients to minimise any loss of data resulting from patient transfer or death. Staff will also visit gastroenterology units to extract data from secondary care patient records. All participants will be followed up for 6 months. Using data extraction templates, adapted from those developed by us for previous comparable studies, we will collect the information shown in Table 2.

**Table 2 Tab2:** The type of data collection from the two care sites

Primary care data collection
Demographic data
Date of first consultation
Duration of index (first) consultation
Dates of subsequent consultations before referral
Referral in the episode of care – Y/N
Type of referral (2WW; open access gastroscopy; routine out-patient department; emergency, other)
Date of referral
Co-morbidities
RAT used - Y/N
Date used
Duration of consultation when RAT used
Final diagnosis
Secondary care data collection
Type of referral (2WW; OAG; routine OPD; emergency, other)
Diagnosis
Date of diagnosis
Stage

Practice level data on direct-to-gastroscopy referral and conversion rates will also be collected. The East Midlands Knowledge and Intelligence Team will hold cancer waiting time data at the practice level on upper gastrointestinal (GI) 2WW referrals, conversion and detection rates, and emergency presentations.

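### Participation percentage by arm cannot show whether the eRAT has altered who is recorded, found and judged eligible, so the low-risk statement covers selective invitation only

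*Protocol article*

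**What the plan says.** All references are to the protocol article.

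- **Order of events.** Statistical analysis recognises possible "recruitment bias resulting from randomising the practices before recruiting patients to the trial". It nevertheless states "we consider the risk of serious recruitment bias to be low because all eligible participants from intervention or control practices will be invited", and adds that invitations are posted once the index consultation is over.
- **Check.** The same section reports, by arm, the percentage of eligible patients who are recruited. It also records the number of eligible patients in each arm, but gives that count no role in detecting bias.
- **Identification.** Under Patient recruitment, administrative staff "search their electronic medical records weekly in order to identify patients who have presented to a GP within the previous week with qualifying symptoms". A GP or practice research nurse then reviews the list for eligibility. Sample size assumes that READ codes will identify 80 % of patients with the index symptoms.
- **Tool.** Under Intervention, the calculator is opened at the GP's discretion. "It allows additional symptoms to be entered and generates a value for the risk of a currently undiagnosed G-O cancer". The tool "will also display an on-screen prompt at the start of a consultation" when symptoms entered in the previous 12 months carry a total risk above 2 %. Only intervention practices receive the implementation visit with instruction on using the eRAT.
- **Analysis.** The first comparison listed is whether the patient is referred, among all patients. Estimates are crude, and adjusted for region and practice size.
- **Practice-level data.** "Practice level data on direct-to-gastroscopy referral and conversion rates will also be collected". Upper GI 2WW referral data at practice level are held by an external intelligence team.

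**The concern.** Being invited is the last step of entry to this trial. Before it, a symptom must be recorded, the record must be found by the search, and the patient must be judged eligible. All three happen after randomisation, and the first happens in the consultation where the tool may be in use. Both reasons given for low risk (everyone eligible is invited, by post, afterwards) concern the last step only. Posting the invitation after the consultation protects against selective approach by the GP. It does not protect identification, which by then already follows exposure to the tool.

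If the intervention arm finds additional patients whose chance of referral differs from that of the others, the referral comparison mixes a change in GP behaviour with a change in who is counted. Outcomes nested in referred patients can be affected too. The arm comparisons supply the preliminary effect estimate, which Trial objectives and Sample size want as evidence for phase III. A reassuring participation percentage would be read as support for that estimate although it carries no information on this route.

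**Working it through.** **1. The plan's own yield.** Inputs from Sample size: 30 practices per arm, 1800 patients aged 55+ per practice, 16 months, 80 % identifiable through codes, 80 % consent, 28–40 new upper GI symptoms and 17 gastroscopies per 1000 per year, 4 % cancer yield.

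- Person-years per arm: 30 × 1800 × 16/12 = 72,000.
- Participants: 72,000 × 0.80 × 0.80 × 0.028 = 1290 and × 0.040 = 1843 (stated 1292–1843).
- Gastroscopies: 72,000 × 0.64 × 0.017 = 783 (stated 780). Cancers: 783 × 0.04 = 31 (stated 32).

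The figures reproduce to rounding, so these inputs describe the plan's model of recruitment. That model leaves 20 % of symptomatic patients unidentified, which is the room in which the arms could differ.

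**2. What the participation percentage responds to.** Let N be the number of symptomatic patients in an arm and c the share recorded, found and judged eligible. Then eligible = N × c, recruited = N × c × 0.80, and participation = (N × c × 0.80)/(N × c) = 80 % for every c.

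**3. What the eligible count responds to.** Eligible = 72,000 × rate × c. Control has c = 0.80. Values of 0.85–0.95 for the intervention arm are assumptions. The ratio to control runs from 0.85/0.80 = 1.06 to 0.95/0.80 = 1.19.

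**4. What could happen to the referral odds ratio with no true effect.** Gastroscopy stands in for referral, so the control proportion is p = 17/28 = 0.607 or 17/40 = 0.425. Let r be the referral risk of the extra patients relative to the others (assumed). The intervention proportion is p × [0.80 + (c − 0.80) × r]/c.

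Example with p = 0.607, c = 0.95, r = 0.5: 0.607 × 0.875/0.95 = 0.559, and OR = (0.559/0.441)/(0.607/0.393) = 0.82.

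Example with p = 0.425, c = 0.95, r = 1.5: 0.425 × 1.025/0.95 = 0.459, and OR = (0.459/0.541)/(0.425/0.575) = 1.15.

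In each OR cell the first value uses p = 0.607 and the second p = 0.425.

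| c, intervention arm | Participation | Eligible at 28/1000 | Eligible at 40/1000 | OR, r = 0 | OR, r = 0.5 | OR, r = 1 | OR, r = 1.5 |
|---|---|---|---|---|---|---|---|
| 0.80 | 80 % | 1613 | 2304 | 1.00 | 1.00 | 1.00 | 1.00 |
| 0.85 | 80 % | 1714 | 2448 | 0.86 / 0.90 | 0.93 / 0.95 | 1.00 | 1.08 / 1.05 |
| 0.90 | 80 % | 1814 | 2592 | 0.76 / 0.82 | 0.87 / 0.91 | 1.00 | 1.15 / 1.10 |
| 0.95 | 80 % | 1915 | 2736 | 0.68 / 0.75 | 0.82 / 0.87 | 1.00 | 1.23 / 1.15 |

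The participation column never moves and the eligible counts do. The odds ratios show only that the sign depends on r, on which the document is silent.

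**5. Adjustment.** Region and practice size are practice-level variables. They do not correct a difference between arms in which patients were identified within practices.

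**The case against.** The strongest reply is that the mechanism is possible but undocumented, and much of it stands.

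- A reader might infer that the eRAT does change coding. Nowhere does the article say so, or say that calculator entries are written to the record as searchable codes.
- The prompt fires only above 2 % risk and on symptoms already entered, so prompted patients may be findable in either arm. Additional symptoms may go to patients who already qualify.
- The exclusion for new prescriptions issued for other reasons suggests that the search may also pick up prescriptions, which would reduce its dependence on symptom codes.
- A reader might infer that extra patients would be low risk and dilute referral. The document gives no basis for that: a tool aimed at raised risk could as well bring in higher-risk patients.
- A reader might infer that the control-arm referral proportion, named under Process and outcome measures as a phase III planning input, is biased. It comes from practices without the active tool, so this route does not distort it.
- The comparisons are ancillary in a trial not powered for hypotheses. The plan already records eligible counts by arm, describes baseline demographics by arm and collects practice-level data.

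These points limit the size of the concern and leave its core intact. The low-risk statement is affirmative, and its reasons do not reach identification. The named check is blind to it by construction. The information that could show it is planned but not assigned to this use.

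**Conclusion.** The concern holds in conditional form. The tool and its training visit may change who is recorded, found and judged eligible in the intervention arm. Neither universal postal invitation nor the participation percentage addresses this.

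The blindness of the percentage is exact and rests on no assumed coding effect. The 6–19 % rise in eligible patients and the odds ratios in the table rest on assumed values of c and r, with gastroscopy standing in for referral and consent at 80 % in both arms. They are illustrations, and at r = 1 there is no bias. That reviewing staff know the allocation is inferred from delivery of the tool at practice level.

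The consequence is confined to the preliminary effect estimates and how they are read. It does not make the trial unsound. It does not require practice-level rates to become the leading comparison, since the trial has no lead comparison. A reader might also want to adjust for presenting symptom. That would be unwise, because the tool may itself affect the recorded symptom, and Table 2 does not list it among the data extracted. The plan should be changed, at small cost.

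**What to change.** In Statistical analysis:

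1. Add a by-arm comparison of eligible patients per 1000 registered patients aged 55+ (or per list size) per practice-month. Where practices can supply counts, do the same for search-identified patients. Aggregate counts are enough, since the research team has no access to the practice databases. Read the result descriptively: equal rates do not prove that the same kind of patient was found.
2. Compare the age and sex of recruited patients by arm, and add an age- and sex-adjusted sensitivity estimate. Take both from the Table 2 demographic extraction, because the weekly age-group and gender returns are described for the intervention arm only.
3. Present the practice-level 2WW and direct-access gastroscopy referral rates by arm alongside the patient-level comparisons, as a check that does not depend on study identification or consent.
4. Limit the low-risk statement to selective invitation, and note that identification bias remains possible.

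The cost is a list-size denominator per practice (practice size is already an adjustment variable), a short table and a few sentences. One drawback is that practice-level data may not split at age 55, which would blunt the check in item 3.

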## Background

For most cancers, only a minority of patients have symptoms that meet the National Institute for Health and Clinical Excellence (NICE) guidance for urgent referral [1, 2]. For gastro-oesophageal (G-O) cancers, the ‘alarm’ symptoms of dysphagia and weight loss are reported by only 32 and 8 % of patients, respectively [3], and their presence correlates with advanced-stage disease [4]. Several other symptoms predict G-O cancer but with absolute risks in the region of 1 %. Not surprisingly, therefore, delays in diagnosis may occur; 25 % of oesophageal and 36 % of gastric cancer patients visit their GPs three times or more before diagnosis [5]; only 34 and 23 %, respectively, are referred by the 2-week wait (2WW) pathway for urgent referral of patients with suspected cancer; and 22 and 33 %, respectively, present as emergencies [6].

The primary investigation for G-O cancer is gastroscopy, whether by 2WW or direct-access referral. One solution to a diagnostic delay may be to investigate more patients. General practices in the lowest tertile of the gastroscopy referral rate (6.2/1000 per annum (p.a.)) have worse outcomes (emergency admissions, 6-month mortality) than practices in the highest tertile (16.4/1000 p.a.) [7]. Patients 55 years of age and older account for 65 % of all gastroscopies, and the gastroscopy rate in this age group is 17.5/1000 p.a. [8]. Gastroscopy rates are much higher in mainland Europe [9], probably contributing to the observed better survival. However, because gastroscopy is a costly and invasive procedure, any increase in activity should target those patients most likely to benefit.

Recent studies, including those by the co-authors, have provided robust estimates of the risk of several cancers (including G-O) for the symptomatic patient in primary care [3, 10–15]. From these, risk-assessment tools (RATs) have been developed for use in general practice [16–18]. In a feasibility study, their use was associated with increases in 2WW referrals, use of investigations, and new cancer diagnoses [19]. They have now been developed in an electronic clinical decision support (eCDS) format by Macmillan Cancer Support using the BMJ-owned Informatica platform and integrated with some GP clinical computer systems.

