## Trial objectives

The objectives of this trial are provided below:To optimise an intervention based on the use of the G-O cancer eCDS tool, establish its acceptability, and collect relevant data to inform the design of a subsequent definitive phase III trial.To obtain preliminary evidence on the effectiveness, implementation, and cost-effectiveness of the G-O cancer eCDS tool.

At the end of this phase II trial, we will have optimised the intervention and established its acceptability [25]. We will have also generated new knowledge on the process outcomes of the eCDS in primary care and its impact on resource utilisation and healthcare costs. In a subsequent phase III trial, we will examine the effect of the eCDS on G-O cancer stage at diagnosis, on surgical treatment, and on survival.

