### Health economic analyses

First, we will *map out the potential impacts of the eRAT tool from a health economic viewpoint* by determining the places in the clinical pathway where the eRAT may impact the cost to the NHS and the benefit to patients (quality-adjusted life year (QALYs)). These will include the following:A change in the GP consultation length and use of eRATs that may impact GP costsA change in the stage at diagnosis and survival through earlier diagnosis that may impact QALYs and costsA change in the rates of diagnosis via primary care as opposed to emergency presentation that may impact diagnosis costsA change in the number of persons without cancer referred to secondary care that may impact diagnostic costs.

Second, we will *estimated health economic outcomes*. A simple health economic model will be developed using the eRAT impacts mapped out and populated by cost estimates obtained from published literature and other sources. Health economic outcomes generated will include the 2WW referral and gastroscopy costs associated with the eRAT; the cost per additional cancer case diagnosed; and the cost per emergency presentation avoided. We will also explore data requirements and possible modelling approaches for a health economic evaluation of a definitive trial.

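### Stage at diagnosis is compared only among diagnosed cancers, a group whose size the tool may change; cancers per participant, overall and by stage, should be reported beside it

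*Protocol article*

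**What the plan says.** The list of comparisons in the Statistical analysis section of the protocol article is grouped by denominator. Referral is the only outcome compared over all patients. Cancer diagnosis is compared among referred patients, overall and by route: "Whether the referred patients were diagnosed with cancer (conversion – binary outcome". Stage is compared "For patients diagnosed with cancer○ Stage at diagnosis". No cancer outcome, of any stage, is compared over all participants in an arm. The same section says that the comparisons follow the intention-to-treat principle, are ancillary, and that rare binary events will be given as percentages only.

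On whether the tool may change how many cancers are found, the Background says of the risk-assessment tools: "In a feasibility study, their use was associated with increases in 2WW referrals, use of investigations, and new cancer diagnoses". The Health economic analyses section plans to estimate "the cost per additional cancer case diagnosed". On the window, the Data collection section says: "All participants will be followed up for 6 months".

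On the use of stage later, the Trial objectives section says that in phase III "we will examine the effect of the eCDS on G-O cancer stage at diagnosis, on surgical treatment, and on survival". The Process and outcome measures section leaves the phase III primary outcome open. It will examine how stage relates to treatment with curative intent in order to inform that choice.

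**The concern.** Being diagnosed with cancer during follow-up happens after randomisation and may be affected by the intervention. A comparison restricted to diagnosed patients does not have the protection of randomisation, even when every patient is analysed in the arm of the practice.

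A share among diagnosed cancers has a numerator and a denominator that can both move. If the tool brings extra early cancers into the window, the early-stage share rises although the number of late-stage cancers is the same. If it brings late cancers forward into the window, the share falls although diagnosis is faster. From the share alone, a reader cannot tell which count moved.

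What is at stake is mainly the next trial. The Sample size section justifies the number of cancers as enough for effect estimates that inform phase III, and stage is a candidate for its primary outcome. The weakness also does not shrink as the trial grows.

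**Working it through.** **The plan's own figure.** Inputs from the Sample size section: 30 practices per arm, 1800 patients aged 55+ per practice, 17 gastroscopies per 1000 per year, 16 months, 80% identifiable, 80% consenting, 4% with cancer.
- Gastroscopies per arm: 30 × 1800 × 0.017 × 16/12 × 0.80 × 0.80 = 783 (stated 780).
- Cancers per arm: 783 × 0.04 = 31.3, or 31.7 with 6500 × 0.28 = 1820 patients per practice (stated 32).

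The planned 32 cancers per arm is reproduced to within rounding. The Abstract's 3000 participants give 3000/2 = 1500 per arm.

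**Assumptions.** The article gives no stage distribution and no expected number of extra cancers. Assumed here: 10 early and 22 late in the control arm, and 6 extra cancers in the intervention arm.

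| | Control | 6 extra early | 6 late brought forward |
|---|---|---|---|
| Early / late | 10 / 22 | 16 / 22 | 10 / 28 |
| Early share among diagnosed | 10/32 = 31.3% | 16/38 = 42.1% | 10/38 = 26.3% |
| Early per 1000 participants | 10/1500 = 6.7 | 16/1500 = 10.7 | 6.7 |
| Late per 1000 participants | 22/1500 = 14.7 | 14.7 | 28/1500 = 18.7 |
| All per 1000 participants | 32/1500 = 21.3 | 38/1500 = 25.3 | 25.3 |

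**Extra early cancers.** The share rises by 42.1 − 31.3 = about 11 points. With late counts equal, the odds ratio for early stage is the ratio of early counts: (16/22)/(10/22) = 1.60. The standard error of its logarithm is √(1/10 + 1/22 + 1/16 + 1/22) = 0.503, so the 95% CI is exp(0.470 ± 1.96 × 0.503) = 0.60 to 4.3, before any allowance for clustering. The late-stage rate does not differ.

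**Late cancers brought forward.** The share falls by 31.3 − 26.3 = 5 points. The late-stage rate per 1000 rises from 14.7 to 18.7, a ratio of 28/22 = 1.27. Here the per-participant rate also looks like a worsening that comes from faster diagnosis. It does show that the late count moved and the early count did not.

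**Range.** Over an assumed control early share of about 20% to 40% and 3 to 16 extra early cancers, the apparent shift runs from 5 to 27 points and the odds ratio from 1.23 to 3.67. The late-stage rate is equal between arms throughout.

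**Larger trial.** Take a hypothetical 200 control cancers, 30% early, with 20% more cancers in the intervention arm, all early: 60/200 = 30% against 100/240 = 41.7%. A two-sided 5% test of two proportions would reject with probability about 0.72, ignoring clustering, with the same number of late-stage cancers in each arm.

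**The case against.** The consequence within this trial is small, and that stands. The trial is not powered for hypotheses, the comparisons are ancillary, and an interval of 0.6 to 4.3 leaves an 11-point shift well within noise. The inputs to outcome choice and power that the Process and outcome measures section lists do not include a stage effect. It does not follow that the denominator is harmless, because the Sample size section offers this trial's effect estimates as a basis for phase III.

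Much of the information could be pieced together, and that stands in part. Referral among all patients combined with conversion among the referred gives cancers per participant for referred patients, and the cost per additional case needs cancer yield by arm. Neither is a comparison by stage, and the list does not call for one.

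Per-participant rates do not cure the timing problem, and that stands in full. They too are cut off at 6 months, as the 18.7 against 14.7 shows. The participant denominator is also formed after randomisation: patients are found by a search of coded symptoms and then consent by post. The tool lets a GP enter additional symptoms, which could alter who is found. The Statistical analysis section itself recognises possible recruitment bias and judges the risk low.

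Three stronger readings are tempting, and the documents do not support them:
- A reader might infer that stage is the intended phase III outcome. The Trial objectives section names surgical treatment and survival as well, the Discussion names further outcomes, and the primary is still to be chosen.
- A reader might infer that a higher early-stage share would mean no late-stage cancer was avoided. Participants have symptoms, and the control counterparts of extra early cancers could surface as late disease after 6 months. In that case the shift would be real.
- A reader might infer that per-participant rates should replace the stage share as the measure for phase III. That would exchange one window-dependent measure for another.

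**Conclusion.** The point holds as a gap in the listed comparisons that is cheap to close. Stage is one intended phase III outcome and a candidate primary. It is compared only within a group that the tool may enlarge, and no cancer or stage outcome is compared over all participants. The early-stage share can rise without any difference in late-stage cancers over the window, and can fall through earlier detection of late cancers.

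The sizes, 31% to 42% in one case and 31% to 26% in the other, rest on the assumed 10/22 split, the 6 extra cancers and 1500 participants per arm. They show what the listed analysis cannot distinguish, and do not predict the result. The harm would lie in how the estimate is carried into the design of phase III.

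**What to change.** In the list of outcomes in the Statistical analysis section, add under all patients: all gastro-oesophageal cancers, early-stage cancers and late-stage cancers, each per 1000 participants by arm. Give cluster-robust 95% confidence intervals where counts allow, and otherwise counts and percentages. Report these beside the stage distribution among diagnosed cancers, which stays.

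Add a sentence saying that neither measure alone should be read as the stage effect for phase III, because both depend on the 6-month window and participants are recruited after practices are randomised.

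The cost is a few lines of plan. Diagnosis and stage are already among the items in Table 2, so no new data are needed. The downside is small counts and wide intervals.
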